#### Patient-reported outcome measures

2.3.1

To detect the impact of individual motivation, expectations of rehabilitation and the risk of early retirement, assuming that they have an influence on patient outcome, the following questionnaires will be used: FREM-8, PAREMO-20 and SIBAR. These questionnaires are used in part because of the possibility that patients who are still working may have a hidden desire for early retirement. Patients’ attitude, expectation and goals can, of course, have an impact on the results of rehabilitation.

To detect patients' rehabilitation-related expectation, the FREM-8 will be used. The FREM-8 evaluates in four subscales (expectations about recovery, health, coping with illness, and retirement) on a 4-point graded response scale (0 = not at all true, 3 = exactly true) patients' expectations [19]. The FREM-8 showed an internal consistency of Cronbach's alpha between 0.48 in the health subscale to 0.85 in the retirement subscale [19].

The Patient Questionnaire for Assessment of Rehabilitation Motivation (PAREMO-20) records in six subscales the mental distress, physical limitations, social support and gain from illness, willingness to change, level of information regarding rehabilitation measures, and skepticism [20]. The scales are formed as a sum score of the four level item values (1 = not true, 4 = true). Satisfactory to good internal consistencies (Cronbach's alpha) between 0.59 and 0.88 for skepticism and mental distress were found for the PAREMO-20, respectively [21].

The patient-reported functional outcome and its change during the observation period will be assessed using the well-established 12-Item Short-Form Health Survey (SF-12 [22]) with its mental (MCS) and physical component summary (PCS) subscales, the Oswestry Disability Index (ODI [23,24]) and the Spine Functional Index (SFI [25]). Patients with LSS do not only suffer from back pain. Other disabilities and age can lead to falsification of various items on the established questionnaires such as SF-12 or ODI. For this reason, we try to uncover a better picture of the state of health and the limitations by adding the above-mentioned questionnaires on expectation and motivation and the SFI.

The SF-12 consists of 12 items with responses of two to six-level categories. At 0.77 and 0.80 for the PCS and MCS, respectively, Cronbach's alpha showed good internal consistency [26].

The ODI consists of 10 items with answer options of 5 levels. It detects back pain related functional disability in daily life and was shown to have an overall Cronbach's alpha of 0.90 [24]. However, the greatest functional limitation in LSS patients is the limitation precisely in walking. Also, we expect that because of the anticipated older cohort, the answer to the question of sexual activity might not always be answered adequately.

The SFI is a newer spine-specific questionnaire that overcomes the limitations of existing whole-spine questionnaires and identifies clinical and practical characteristics along with a recognized criterion, the Functional Rating Index (FRI [27]). It showed internal consistency of 0.91 and a high correlation with the FRI of 0.87 [25].

Additionally, the pain medication and the dosage will be recorded according to the WHO grading scheme.

Before functional, balance and gait analyses, patients’ heart rate variability (HRV) will be examined while lying prone to record autonomic nerve activity. After 5 min rest or relaxation time, 5 min of continuous HRV recording will be performed [28]. This will be followed by measurements of the lumbar resting myofascial tone [[29], [30], [31]] with a portable device (MyotonPRO, Myoton AS, Tallinn, Estonia) applied paravertebral at both sides to detect changes in muscle stiffness during the observation period. Thereafter, the following functional assessments will be completed by each participant: functional reach test (FRT), loaded reach test (LRT), handgrip strength, standing balance control (60s in natural position), and gait analysis on an instrumented treadmill (h/p/cosmos sports & medical gmbh, Nussdorf-Traunstein, Germany) with an integrated pressure measuring platform (FDM-THQ-i3, zebris Medical GmbH, Isny, Germany). Patients will be asked to walk at A) 2.5 km/h for approximately 30s, B) self-selected speed as long as possible or up to 6 min (6-min walk test [[32], [33], [34]]) and, after a sufficient break, C) 115% of the self-selected speed again for approximately 30s. Following each walking task, as well as after each functional test performed, patients will be asked to indicate their individual exertion (rate o perceived exertion, RPE [35]) on an 11-point NRS [36]. For an overview of the assessment procedures used in the study, please refer to Fig. 2. The ODI together with the distance walked at self-selected speed were selected as primary outcome measures, whereas strength (handgrip strength) and functional mobility (FRT) served as secondary outcomes. The experimental outcome categories with exploratory variables are listed in Table 2.

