#### Statistical analyses

2.3.7

The data collected will be used to answer various research questions. Hence different analyses will be conducted. First, data quality checking will be performed to ensure that discrepancies, errors, or duplicates are excluded from further analyses and overall data consistency is given. Second, data will undergo exploratory data analysis. Finally, depending on the variables available, appropriate statistical tests (e.g., linear regressions, Student's t-tests, Chi^2^-tests) will be applied to uncover differences related with rehabilitation timing after LSS surgery. Statistical analyses will be performed using IBM SPSS 28.0 (IBM Corp., Armonk, NY, USA) software.a)Subjective (ODI, SF-12) and functional performance (handgrip strength, FRT) of early and later post-operative rehabilitation intervention groups will be compared using multivariate general linear mixed model and Chi^2^-test (categorical data, specifying frequencies in percent).b)Subjective and functional performance of surgically (two groups) and conservatively treated patients with LSS and controls without spinal impairments will be compared using multivariate general linear mixed model and Chi^2^-test (categorical data, specifying frequencies in percent).c)Subjective and functional performance before and after the intervention(s) will be compared using multivariate general linear mixed model and Chi^2^-test (categorical data, specifying frequencies in percent).d)Associations of subjective and functional assessments will be tested by means of correlation analyses.

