#### Patient and public involvement (PPI) statement

2.3.8

Early or delayed start of the rehabilitation program will be randomized for the surgically treated patients. If patients don't want to be randomized, they can choose their preferred starting time of the post-surgical rehabilitation program. Control participants will be recruited through public announcements. Furthermore, patients will be encouraged to recruit controls without any known lumbar spinal impairments from their own environment in order to increase the chance of getting comparable control subjects in terms of sex, age, and activity level. Patients' and controls' will be asked about their experience with the assessments in order to better estimate and compare the exhibited strain and perceived exertion of the functional tests.

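### The early-versus-later comparison mixes randomised patients with patients who chose their timing, and states no adjustment for the motivation and expectation that the protocol assumes influence outcome

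*Protocol article*

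**What the plan says.** Section 2.3.1 of the protocol article gives the reason for three of the questionnaires. Motivation, expectation of rehabilitation and risk of early retirement are measured "assuming that they have an influence on patient outcome, the following questionnaires will be used: FREM-8, PAREMO-20 and SIBAR". The same paragraph ends by saying that patients' attitude, "expectation and goals can, of course, have an impact on the results of rehabilitation".

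Section 2.3.8 describes allocation: "Early or delayed start of the rehabilitation program will be randomized for the surgically treated patients". The next sentence opens a second route: "If patients don't want to be randomized, they can choose their preferred starting time of the post-surgical rehabilitation program". Neither the expected share of choosers nor the randomisation ratio is given.

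Section 2.3.7, item a), sets out the timing analysis. On ODI, SF-12, handgrip strength and functional reach, "early and later post-operative rehabilitation intervention groups will be compared using multivariate general linear mixed model and Chi^2^-test". No covariate is named, randomised and chosen allocation are not distinguished, and FREM-8, PAREMO-20 and SIBAR do not appear anywhere in that section.

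**The concern.** The protocol treats motivation and expectation as prognostic and lets some patients select the exposure under study. A factor that influences both the choice of timing and the outcome confounds the timing comparison among those who chose. Randomised patients are protected from this in expectation, but item a) as written puts both kinds of patient into the same early and later groups.

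An ODI difference between the groups could then partly reflect who wanted early rehabilitation. The trial's main question is about timing, so how the choosers are handled bears directly on how its result can be read.

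**Working it through.** **1. The plan's own figure.** Section 2.3.6 takes a mean ODI change of 16.1 with SD 17.8, so d = 16.1/17.8 = 0.90. A one-sample t-test at 5% with 95% power then needs 15 patients. This reproduces as a one-sided test (power 0.952 at n = 15). Inflation for the 65% who improved by at least ten points gives 15/0.65 = 23.1, rounded up to 24. Inflation for 20% dropout gives 24/0.8 = 30 per group, as stated. The point here does not depend on this calculation; it only borrows the SD and the 24 evaluable patients per group.

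**2. What the sections say together.**
- Influence on outcome: assumed by the protocol (2.3.1).
- Choice of exposure: allowed for patients who decline randomisation (2.3.8).
- Motivation or expectation affecting that choice: not stated anywhere. This is an inference.
- Adjustment or separation in the timing analysis: none stated (2.3.7, item a).
- Possible safeguards elsewhere: section 2.2 monitors preferred timing and unspecified other parameters in periodic meetings, and the Background speaks of predictors of success or failure. Neither adjusts the timing contrast. Item d) of 2.3.7 is a correlation analysis and does not do so either.

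**3. Size under assumptions.** Inputs that the documents do not give:
- p, the share of choosers, taken as equal in both timing groups: 0, 0.5 or 1
- g, the motivation gap between early and later choosers: 0.3 to 0.8 SD
- r, the correlation of motivation with ODI change: 0.2 to 0.4

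Input from section 2.3.6: SD = 17.8.

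Bias with no true timing effect = p × g × r × 17.8.

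| Share choosing | Low (g 0.3, r 0.2) | Middle (g 0.5, r 0.3) | High (g 0.8, r 0.4) |
|---|---|---|---|
| All | 0.3 × 0.2 × 17.8 = 1.1 | 0.5 × 0.3 × 17.8 = 2.7 | 0.8 × 0.4 × 17.8 = 5.7 |
| Half | 0.5 | 1.3 | 2.8 |
| None | 0 | 0 | 0 |

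**4. Against the noise.** If the groups in section 2.3.6 are read as the timing groups, 24 evaluable patients in each give a standard error of 17.8 × √(2/24) = 5.1 points. The middle case with all choosing is about half of that (2.67/5.14 = 0.52) and the extreme case slightly more than one standard error (5.70/5.14 = 1.11). For a two-sided 5% two-sample t-test with 24 per group, the false-positive rate becomes 5.5% to 19.2% if all chose and 5.1% to 8.4% if half did. It stays at 5% if none did. The ten-point change used in section 2.3.6 is a further yardstick.

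**The case against.** The strongest objection is that silence is not a decision. Item a) names outcomes and a model class, and a mixed model can carry covariates. So can the linear regressions in the general sentence, which says that "appropriate statistical tests (e.g., linear regressions, Student's t-tests, Chi^2^-tests) will be applied to uncover differences related with rehabilitation timing after LSS surgery". Covariate lists are commonly left to an analysis plan, and this is a condensed article whose analysis plan is not shown. A reader might infer that the trial has decided against adjustment. The documents do not support that; they only state none.

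The link from motivation to choice of timing is also unstated. The only determinant of timing that the article names is the surgeon's preference in routine regional care (Background). A reader might further infer that motivated patients will choose early rehabilitation and make it look better. Nothing in the text fixes that direction.

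Finally, covariates alone are a partial remedy. FREM-8 has four subscales and PAREMO-20 six, and internal consistency falls to 0.48 (FREM-8 health) and 0.59 (PAREMO-20 skepticism). Adjusting a pooled comparison for two such scores could give false reassurance.

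These objections limit the claim and its size without removing it. The article specifies the timing comparison closely enough to show self-selected and randomised patients in the same groups, while calling unmentioned factors influential. That is more than a missing list of covariates. The last objection strengthens the case for separating the randomised patients.

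**Conclusion.** The point holds in limited form. As written, the timing comparison is open to confounding among patients who chose, by factors that the protocol itself assumes to matter, and no stated step addresses it.

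The size is hypothetical: about 1.1 to 5.7 ODI points if all patients chose, 0.5 to 2.8 if half did, and zero in expectation if none did, with unknown direction. The gaps, correlations and chooser shares are assumptions; only the SD and the group size come from the article. The 5.7-point figure is the extreme corner of the range and should not be read as an expected bias. Nor do the documents show that the timing comparison is invalid, because the randomised patients still support an unconfounded contrast if they are analysed as such.

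**What to change.** In item a) of section 2.3.7:

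- Include a term for randomised versus chosen allocation, and report the timing effect in the randomised patients separately. The separate report is the essential step, since a term for allocation alone still yields one pooled timing effect.
- For patients who chose, adjust for baseline ODI and for one baseline subscale each of FREM-8 and PAREMO-20. Name both before outcome data are seen; expectations about recovery and willingness to change are examples.
- Use only pre-surgery values, because later ones may be altered by treatment. The article does not say whether the questionnaires precede the choice of timing, so this order should be stated.
- Let the inclusion of SIBAR depend on how complete it is in this cohort. The article gives no ground for excluding it outright.

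The cost is wording and no new data. The model loses a few degrees of freedom, and missing baseline questionnaires need simple handling. The randomised-only estimate is less precise: if half of 24 per group were randomised, its standard error would be 17.8 × √(2/12) = 7.3 points instead of 5.1. Residual confounding will remain among choosers, given the low reliability of some subscales and unmeasured reasons for choosing. The adjusted result should therefore stand beside the randomised comparison and not replace it.

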#### Power analysis and sample size considerations

2.3.6

The ODI was set as our primary outcome measure. For this study, we approximated the sample size using a hypothetical approach. In order to estimate the number of cases needed, the ODI results of 46 patients with LSS (41% men) who underwent fusion surgery were used [45]. Considering the mean change from baseline of 16.1 points and the standard deviation of 17.8, a large effect (d = 0.9) can be expected. With a significance level of 5% and a power of 95%, the minimum sample size needed with this effect size is 15 patients with LSS who will undergo fusion surgery [one-sample *t*-test] (G*Power 3.1.9.2). Only 65% (30) of the patients reduced their ODI by at least ten points one year post-operatively [45]. Taking into account that approximately two-third of the patients included will reach the minimum clinically important difference and assuming a relatively high dropout rate of 20%, 30 patients with LSS would have to be initially included in each group.

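### The protocol names two primary outcomes in one section and one in another, and the listed early-versus-later comparison omits walking distance

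*Protocol article*

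**What the plan says.** Three places in the protocol article bear on this.

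- **Section 2.3.1, paragraph on the functional assessments:** "The ODI together with the distance walked at self-selected speed were selected as primary outcome measures", followed by "whereas strength (handgrip strength) and functional mobility (FRT) served as secondary outcomes". The distance comes from a treadmill walk at "self-selected speed as long as possible or up to 6 min (6-min walk test").
- **Section 2.3.6 (sample size):** "The ODI was set as our primary outcome measure". The calculation uses ODI inputs only: "Considering the mean change from baseline of 16.1 points and the standard deviation of 17.8, a large effect (d = 0.9) can be expected". It continues: "With a significance level of 5% and a power of 95%, the minimum sample size needed with this effect size is 15 patients". The section gives no effect, standard deviation or sample size for walking distance.
- **Section 2.3.7 (statistical analyses), item a):** "Subjective (ODI, SF-12) and functional performance (handgrip strength, FRT) of early and later post-operative rehabilitation intervention groups will be compared". Walking distance is not in the list.

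The only significance level in the article is the 5% in Section 2.3.6. The article does not say whether one or both primary outcomes must succeed, and it gives neither a testing order nor a division of alpha.

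**The concern.** Sections 2.3.1 and 2.3.6 cannot both be right about the primary outcome. A reader of the final report could cite either one as the prespecified position, so emphasis could shift to whichever outcome looks better.

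Item a) adds to the difficulty. It is the comparison that answers the trial's main question on rehabilitation timing. It names both secondary outcomes, and also SF-12, which Section 2.3.1 places in neither tier, but it leaves out a declared primary. The omission matters because the Background treats walking distance, alongside pain, as the leading functional outcome in this disease.

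If two outcomes really are primary, the one 5% level has to be tied to a success rule before the type I error or the power of the trial can be stated.

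**Working it through.** **1. The three sections side by side**

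| Outcome | Section 2.3.1 | Section 2.3.6 | Section 2.3.7 item a) |
|---|---|---|---|
| ODI | primary | primary; basis of sample size | listed |
| Distance at self-selected speed | primary | not mentioned | not listed |
| Handgrip strength | secondary | not mentioned | listed |
| Functional reach test | secondary | not mentioned | listed |
| SF-12 | neither tier | not mentioned | listed |

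**2. The plan's own sample size**

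Inputs from Section 2.3.6: mean ODI change 16.1, SD 17.8, 5% level, 95% power, one-sample *t*-test.

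- Effect size: 16.1 / 17.8 = 0.904, stated as 0.9.
- Exact noncentral-*t* power with d = 0.9 and a one-sided 5% level: n = 14 gives 0.938 and n = 15 gives 0.952. The stated 15 is reproduced.
- With a two-sided 5% level, n = 15 gives 0.899 and the requirement is 19. So 15 corresponds to a one-sided test, although the section does not state sidedness.
- Inflation for the responder share and 20% dropout: 15 / (2/3) / 0.8 = 28.1, or 15 / 0.65 / 0.8 = 28.8. The stated 30 per group is consistent with rounding up.

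Walking distance enters at no step, so the stated power is a statement about ODI only.

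**3. If both outcomes are primary and either one is enough**

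This rule is an assumption. With each outcome tested two-sided at 5%:

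- Independent outcomes: 1 − (1 − 0.05)² = 1 − 0.9025 = 0.0975.
- Correlated outcomes: 1 − P(|Z1| < 1.96 and |Z2| < 1.96) for a bivariate normal. The correlations are assumed, because the article gives none.

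| Correlation | Family-wise error |
|---|---|
| 0 | 9.75% |
| 0.3 | 9.5% |
| 0.5 | 9.1% |
| 0.7 | 8.3% |
| 0.9 | 7.0% |

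An equal split of alpha (2.5% each) would remove the inflation. On the plan's own one-sided calculation with d = 0.9, power for ODI at n = 15 would then fall from 0.952 to 0.899, and 19 patients would be needed before inflation. That is 19 / (2/3) / 0.8 = 35.6 or 19 / 0.65 / 0.8 = 36.5, so 36 to 37 per group in place of 30.

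**4. If both outcomes must succeed**

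Each can be tested at the full 5% without inflation. The cost is in power: if each had 95% power and they were independent, joint power would be 0.95 × 0.95 = 0.90. Power for walking distance cannot be computed from the article.

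**The case against.** The strongest reply is that this is a condensed article. A multiplicity rule and the full model specification commonly sit in an analysis plan that is not shown, so their absence is no fault. That stands, and it limits the point in four ways.

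- **Error inflation.** A reader might infer that the trial runs at nearly 10% type I error. The article never says that success on either outcome suffices, and its wording fits a both-must-succeed rule equally well. The 9.75% is conditional and an upper figure.
- **Walking distance never tested.** A reader might infer this from item a). Section 2.3.7 also foresees other suitable tests for differences related to rehabilitation timing, and items b) and c) refer to functional performance without a list. The supportable claim is narrower: walking distance is not named in the list for the timing comparison.
- **Table 2.** Walking distance is missing from it, but so is ODI, and the table is introduced as holding exploratory variables. Its omission there shows nothing.
- **A joint test that decides.** The term multivariate might suggest that a joint test across outcomes settles success. The article does not say so, and such a model can give outcome-specific estimates.

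The reply does not reach the core. An article may leave detail to another document, but it should not state one primary outcome in one section and two in another. An unseen plan cannot make both published statements true.

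**Conclusion.** The point holds as a contradiction about the primary outcome, together with the omission of one declared primary from the listed early-versus-later comparison. Both are explicit in the text and need no assumption.

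The numerical consequence is conditional. Under an either-outcome rule with each test at 5%, the family-wise error lies between 7.0% and 9.75% over assumed correlations from 0.9 down to 0. Under a both-outcomes rule it is not inflated, but joint power is lower. If ODI is the sole primary, neither consequence arises and the stated 30 per group is unaffected by this point.

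The documents do not support saying that the trial has chosen to run without error control, nor that it will leave walking distance unanalysed.

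**What to change.** Reconcile Sections 2.3.1, 2.3.6 and 2.3.7 before outcome data are analysed, and add distance walked at self-selected speed to the outcomes in item a). Two resolutions are coherent:

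1. **ODI as sole primary.** This matches the sample size section. Walking distance becomes the first key secondary, tested at 5% only if ODI is significant. No alpha split is needed and 30 per group is unchanged. The cost is that walking distance loses primary status, although the Background gives it high importance.
2. **Both outcomes primary.** State whether either or both must succeed and how alpha is handled, and say that the stated power applies to ODI only. The cost is less favourable power, through either the alpha split or the joint requirement.

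Under either resolution, report from the mixed model a between-group estimate specific to each primary outcome.

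Most of the work is wording. But Section 2.1 says that baseline data collection began in August 2023, so the change should go through the amendment and registry update that the article's ethics statement already provides for, with its date recorded.
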